### Step 2: search for literature evidence to test initial program theories

In Step 2, we will complete a realist synthesis of relevant literature to test, refute, and refine our IPT. The synthesis will be and reported in line with the RAMESES (Realist And Meta-narrative Evidence Syntheses: Evolving Standards) publication standards for the realist synthesis (51). A realist synthesis is a theory-driven approach to synthesise the literature for empirical evidence to generate insights into complex interventions or programs and how they work in specific contexts (52). In contrast to traditional systematic reviews, realist synthesis attempts to gain a deeper understanding of the underlying mechanisms, contextual factors, and interactions that shape outcomes (51). Realist synthesis aim to answer not only the questions of “what works” but also “how, for whom, and under what circumstances” (42). Based on the realist synthesis interpretative, theory-driven approach, we will iteratively search for qualitative, quantitative, and descriptive literature to understand and unpack the underlying generative mechanisms (M) that explain “how” outcomes (O) are caused and the influence of context (C). We will follow the methodological steps outlined in Figure 2 to complete and report our synthesis based on RAMESES publication standards (51).

**Figure 2 F2:**
[figure not shown]
Realist synthesis steps.

Refined program theories are intended to highlight the underlying generative mechanisms that contribute to the effectiveness of the rapid response team model in effectively addressing MSD. In addition, theories will consider the contextual factors that influence the implementation and effectiveness of the response model (53). The refined program theories resulting from the synthesis will be shared with the program designers within the organisation as part of the theory gleaning process. This collaborative step involves engaging with the program designers to examine and evaluate the refined theories to determine and prioritise theories for further testing in the next stage of the evaluation (51, 53). Program designers will review and provide input on the refined program theories during the theory gleaning process. Based on their expertise and knowledge of the intervention, they will evaluate whether theories are aligned with their initial assumptions and expectations (54). The objective is to gain deeper insights from program designer perspectives and determine which theories are most plausible and worthy of further testing. Through this collaborative engagement, the program designers can contribute valuable insights and identify potential additional contextual factors, mechanisms, or outcomes (53, 54). Discussions and feedback gained from the theory gleaning process will assist in refining the theories further, identifying additional contextual factors, mechanisms, and outcomes, and planning the design of data collection methodologies for the next phase (52, 54). Refined program theories are intended to highlight the underlying generative mechanisms that contribute to the effectiveness of the rapid response team model in effectively addressing MSD. In addition, theories will consider the contextual factors that influence the implementation and effectiveness of the response model (53).

### Step 3: gather evidence based on initial theories

As part of the realist evaluation methodology, researchers are guided by initial program theories (IPT) when selecting the appropriate instruments and measurement tools (48). As a basis for testing and refining the program theories, IPT's serve as a framework for identifying and collecting relevant data, such as interviews, observations, surveys, and document analyses (46, 55). The realist approach offers the advantage of integrating the strengths of both positivist and constructivist research paradigms. The positivist approach facilitates the collection of empirical evidence on program effectiveness, identifying patterns and quantifying the relationships between inputs, processes, and outcomes (34, 40). On the other hand, the constructivist approach provides rich contextual information, examines the perspectives and experiences of individuals and groups, and uncovers the underlying mechanisms and causal processes (34, 41). By embracing the complexity inherent in healthcare research, the realist methodology offers a sophisticated and nuanced understanding of research problems and questions, leading to comprehensive and insightful findings (56).

### Quantitative data collection

The DIvERT (De-scalation, Intervention, Early, Response, Team) intervention will be trialled in specific clinical settings within a tertiary teaching hospital in Melbourne, Australia. The clinical settings offer unique contexts that encompass differences in patient characteristics, presentations of MSD, and staff's experiences in managing patient deterioration. As part of the healthcare organisation's MSD monitoring and reporting process, electronic medical records, risk management systems, incident reporting systems, and security reporting systems are all used to collect MSD data. We will carry out a quantitative analysis of patient MSD data to gain a better understanding of the “what is going on” phenomenon by examining a range of variables, including but not limited to the patients' demographic characteristics, medical histories, factors contributing to MSD, how the MSD episodes were managed, and any interventions or treatments provided during the DIvERT responses. The analysis is also aimed to assess and establish the outcomes of patients who experience MSD, such stabilisation of MSD, length of stay in hospital, recurrent MSD episodes, and long-term management plans such as behavioural management plans for patients with complex MSD.

It is noted that, a current challenge faced by healthcare organisations is the lack of reliable systems for collecting quality data to inform continuous monitoring and improvement (17). Reporting MSD incidents serves as a foundation for promoting patient safety, facilitating data-driven decision-making such as supporting the implementation of interventions like DIvERT, advancing research efforts, ensuring regulatory compliance, and fostering a culture of continuous improvement in clinical practice (4, 57, 58). By complying with reporting requirements, healthcare systems establish accountability and promote transparency, ultimately enhancing the overall quality of care provided.

### Incident reporting systems

The organisation uses multiple incidents reporting databases, including Code Grey, DIvERT, electronic incident reporting forms, and security reports. These incident reports serve as the basis for testing different theories, such as theories relating to the prompt intervention, multidisciplinary collaboration, early warning signs recognition, tailored interventions, and clinical skills development. By analysing incident reports within these theoretical frameworks, we hope to gain insights into the effectiveness of DIvERT and understand how different factors, such as timing of interventions, collaboration between response team and ward staff, recognition of warning signs, and person centred approaches to managing MSD, contribute to the effectiveness of DIvERT.

Incident analysis is undertaken to uncover the key factors influencing outcomes, including effective and timely intervention preventing MSD risks from escalating to Code Grey, positive patient and staff experience, and positive organisational culture. These incident reporting systems capture comprehensive data, including demographic details, incident specifics, contributing factors, and immediate actions taken. Additionally, they are part of the organisation's risk management and clinical governance efforts, providing data on interventions, response outcomes, and follow-up plans for continuous improvement in patient and staff safety.

### Electronic medical records

We will use electronic medical records to collate data missing from DIvERT, Code Grey, and security data records. Electronic health records will provide valuable insights into how the response team addresses individual patient characteristics and needs in managing MSD and the outcomes of patients presenting with MSD. In addition, the records will provide insights into how the response team considers and manages social, environmental, and other factors that may affect the patient's mental state. The evaluation is also aimed to test theories related to shared decision-making and handover, including patient involvement, and the provision of resources to support staff in caring for patients following an episode of deterioration.

### Staff survey

We intend to survey clinical staff who work in the medical units where DIvERT is being trialled. The survey will enable the collection of self-reported data on variables such as training, confidence levels, and factors affecting communication, assessment, and documentation, providing insight into the perspectives and experiences of nurses. Additionally, we are interested in assessing staff ability to recognise early warning signs of patient MSD and understanding through free text responses, the contextual factors of what should be in place for DIvERT to be effective. Using the survey as a theory confirmatory approach, the objective is to empirically test, refine, and validate the underlying assumptions and causal mechanisms for evidence that best explains how an intervention works (34, 59). This ensures that the theories are grounded in empirical evidence and can inform effective decision-making and program improvement. The survey methodology is preferred for its systematic and efficient nature, which allows for the collection of valuable data from the participants (60).

Based on IPT's we will develop a survey instrument in line with the principles and criteria for designing survey questionnaires to test and refine our theories (61). Survey data will be collected and managed using REDCap electronic data capture tools hosted by the healthcare organisation. Additionally, we will provide a printed copy of the survey instrument for staff to complete to increase uptake. We will complete a pilot test of the survey instrument with select nurses to ensure consistency, clarity, and readability, as well as to check for technical issues, evaluate response options, assess question relevance, and ensure clear instructions.

### Data recording procedure and sample size

A Microsoft Excel spreadsheet will be designed to collect and analyse the variables that have been previously discussed to test and refine our theories. In line with the realist evaluation approach, the data collection methods employed will be comprehensive enough to capture both intended and unintended outcomes and the contextual factors and mechanisms that influenced them (46). Our objective is to audit retrospective data for a minimum period of 6 months which should allow for the thorough analysis of MSD trends, interventions, patterns, and outcomes. However, if the sample size is deemed insufficient, we will extend the data collection period beyond 6 months to ensure rich enough data and an adequate sample size for analysis.

### Qualitative data collection

Qualitative data collection methods, such as interviews and field observations, will offer valuable insights into the underlying mechanisms, contextual factors, and staff experiences that contribute to the effectiveness of DIvERT (37). By engaging with clinical staff in the selected settings and observing real-time interactions, qualitative data collection enables a deeper understanding of how DIvERT operates, how interventions are implemented, and how they impact patient outcomes. Qualitative data captures rich narratives, perspectives, and nuances that quantitative data alone may not fully capture. Qualitative data collection methods provide a comprehensive and holistic view of the complex dynamics involved, helping to uncover the “how” and “why” behind the outcomes observed, and informing recommendations for improving DIvERT (42).

### Interviews

The purpose of the theory refinement interviews is to facilitate direct engagement with clinical staff and gather firsthand accounts, thoughts, feelings, and motivations, uncovering underlying beliefs, assumptions, and values that shape their experiences and decision-making processes regarding DIvERT. Furthermore, interviews will allow participants to share their feedback, suggestions, and concerns regarding DIvERT. According to Manzano (54), the semi-structured interviews should gather the interviewees’ stories about the program because those experiences can provide insights into the program's varying processes (mechanisms, contexts, and outcomes). This teacher-learner cycle's approach should be adopted with theories placed before the respondents to comment on, confirm, deny, and refine the theories (49). An interview guide will be developed to guide the interviews. Table 4 includes examples of some of the questions we intend to ask staff to confirm, disconfirm, and refine our IPT.

**Table 4 T4:** Examples of interview questions.

Open ended question	Can you describe a specific incident involving DIvERT and its impact on managing mental state deterioration? How do you perceive the role and effectiveness of DIvERT in addressing mental state deterioration incidents?
Probing questions	What factors do you believe contribute to the success or challenges faced by staff in assessing early warning signs of mental state deterioration? Can you share any specific examples where the response team's intervention made a significant difference in patient outcomes?
Reflective questions	Looking back, what do you think could have been done differently to improve the effectiveness of DIvERT in managing mental state deterioration presentations? How do you think DIvERT could be adapted or applied in different clinical settings?
Feedback questions	Based on your experiences, what recommendations do you have for enhancing training and preparedness of staff in managing mental state deterioration on the ward? Are there any additional resources or support systems you believe would enhance effectiveness of DIvERT?

### Who will be interviewed?

Clinical staff members participating in the DIvERT pilot program, including nurses, nurse managers, and allied health staff such as social workers, psychologist, and DIvERT team members will be interviewed. Interviews will be conducted face-to-face or virtually via the Microsoft Teams platform and recorded using a recording device. Manzano (54) suggests that realist inquiries should strive to collect a substantial amount of data. Using the purposive sampling technique, we will select participants based on their potential to contribute to refining the initial program theories (47).

For this evaluation, we anticipate conducting between 20 and 30 interviews, as suggested by M Mason (62). However, we will use saturation as our guiding principle during data collection. Saturation is achieved when additional data no longer yield new insights or information relevant to the research themes. In our study, while interviews will test predefined program theories, we will remain open to new emerging themes. We will continually code and analyse the data, closely monitoring theme development as more interviews are conducted. Regular reviews of themes and codes will be performed to ensure both depth and breadth in the data collected. Saturation will be considered reached once the data begin to repeat, with no new information contributing to the data collection process.

### Field observations

Observational research methods are essential for understanding people's actions, roles and behaviours in their natural environments (63). Field observations will involve gathering rich contextual data that complements interviews, surveys, and document analysis. The field observations are aimed to understand the “what is going on” phenomena (64, 65). The researcher will attend DIvERT activations on the medical wards as an observer to see how DIvERT functions in real time and to note the interaction patterns among healthcare professionals, including how they communicate and coordinate to meet MSD needs. Additionally, we will track the timeliness of responses, from the initial call to the team's arrival and their subsequent interventions. We will also monitor immediate patient outcomes post-DIvERT to observe any changes in the patient's mental state. Furthermore, we will identify challenges and barriers that impact the effective functioning of DIvERT.

The researcher will take field notes to document the events and activities that occur during the response calls. The data gathered through field observations can provide valuable insights for refining the DIvERT model, identifying areas for improvement, and informing recommendations for enhancing the management of patient MSD incidents. We aim to complete sufficient, but not exhaustive, field observations to gather data to test and refine the theories. We will follow the principles of reasonable judgment and determine the point of reaching contextual richness (51). Once it is determined that attending additional field observations will not yield new information, we will conclude the field observations.

### Step 4: configuring collected data about initial theories: data synthesis

In realist methodology, the purpose of data analysis is to uncover the underlying mechanisms and contextual factors that influence program outcomes through a confirmatory theory building theory-building approach (42, 46). To draw inferences from the evidence, the primary approach of constructing confirmatory theories, particularly within realist research, is retroductive reasoning (or abductive reasoning) (66). Analysis involves cross-examining program theories with collected data and using theories to understand configurations in data (34). Data analysis is aimed not merely to summarise and report themes in the data, nor is the approach designed to aggregate data by strength in numbers philosophy. Rather, it involves data analysis to improve an ontologically deep understanding of the phenomena being studied (38).

### Quantitative data analysis

Microsoft Excel and STATA (Statistics and Data) will be used to process, organise, and analyse quantitative data. The main objectives of the quantitative data analysis are to:
1.Summarise and present data using descriptive statistics and display data as frequency tables, and diagrams.2.Test if there are differences in Code Grey responses before and after DIvERT intervention implementation.3.Analyse patient outcomes associated with mental state deterioration.

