• Improved model of care for patients presenting with MSD in medical settings. • Improved mental health outcomes for patients in medical settings, including integrated care, timely intervention and treatment, reduced hospital admissions, and improved overall mental well-being for patients. • Implementation of standardised protocols for managing MSD, ensuring consistency and effectiveness approaches through DIvERT. • Reduced incidence of Code Grey and Code Black. • Increased safety for both patients and healthcare staff by addressing potential risks associated with MSD in a timely and effective effort. • DIvERT will present an opportunity to trial an evidence-based model of care for managing MSD for other wards to implement. This is done by refining the DIvERT program theory given contextual factors. • Improved patient and family experience of high-quality hospital care. • Build staff capability and confidence in recognising and managing MSD. • Opportunities for continuous quality improvement through ongoing evaluation and refinement of DIvERT's protocols and interventions. • Develop a cultural change shift and nursing empowerment for managing mental state deterioration. • Positive effects on the well-being of healthcare staff, as they will feel better equipped and supported in managing challenges, potentially reducing stress and burnout associated with managing MSD.

DIvERT, De-escalation Intervention Early Response Team.

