## Method

### DIvERT intervention

The DIvERT is designed for health professionals to intervene at the first sign of MSD and mobilise a timely response to manage the patient's MSD. This early intervention strategy is intended to ensure that the patient receives an appropriate and timely care plan and for the team to manage deterioration and prevent associated risks from escalating. DIvERT will be piloted in two selected clinical settings of an Academic Health Science Centre of a teaching hospital: a trauma unit and an acute surgical ward specialising in burn services; plastics; reconstructive surgery; and ear, nose, and throat surgery. DIvERT was commenced end of 2019 however, due COVID the pilot was stopped. The trial recommenced in 2021. Following implementation, if successful, DIvERT will form part of the hospital escalation response process for MSD, as illustrated in Figure 1.

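### The before/after test of Code Grey has no concurrent comparator and no clean baseline for the restarted trial, so on its own it cannot attribute a change to DIvERT

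*Protocol article*

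**What the plan says.** Step 4 of the protocol article, under Quantitative data analysis, lists three aims. The first is descriptive summary. The second is "Test if there are differences in Code Grey responses before and after DIvERT intervention implementation". The third is "Analyse patient outcomes associated with mental state deterioration", with no comparison stated. Only the second is worded as a test of a difference tied to the intervention.

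The Method section on the DIvERT intervention gives the setting: "DIvERT will be piloted in two selected clinical settings of an Academic Health Science Centre of a teaching hospital". It also gives the history: "DIvERT was commenced end of 2019 however, due COVID the pilot was stopped. The trial recommenced in 2021". The article mentions no concurrent comparison ward.

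On the time span, the section on data recording and sample size says "Our objective is to audit retrospective data for a minimum period of 6 months", and adds that "if the sample size is deemed insufficient, we will extend the data collection period beyond 6 months". It gives no calendar dates for either side of the comparison.

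Table 1 in the Background lists among the intended outcomes "Reduced incidence of Code Grey and Code Black". On data sources, the section on incident reporting systems says "The organisation uses multiple incidents reporting databases, including Code Grey, DIvERT, electronic incident reporting forms, and security reports".

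**The concern.** A before/after comparison without a comparator assumes that nothing else relevant changed between the two periods. The article's own timeline makes that hard to accept, because a pandemic falls between the first start and the restart. The Background names prolonged isolation and restricted visiting among the triggers of mental state deterioration. By the article's own account, then, conditions typical of that period could move the outcome in the absence of any intervention.

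The earlier run adds a second difficulty. Once DIvERT has been started and stopped, the time before implementation no longer has one meaning. The months before the 2021 restart are not DIvERT-naive if the same settings took part in the first run.

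What is at stake is the reading of the one stated test. Lower Code Grey incidence is an intended outcome. The abstract and the Conclusion say that the evaluation will inform on effectiveness. A background shift could look like a benefit of DIvERT or could hide one.

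**Working it through.** **1. Is there a stated figure to reproduce?** No. The article gives no Code Grey count, rate, effect size or sample size for this test. The point rests on the design and the timeline. The arithmetic in step 3 only illustrates it.

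**2. Which baselines are possible?** From the dates in the Method section:

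| Before | After | What lies between or within |
|---|---|---|
| (a) Before end of 2019 | After the 2021 restart | First run and COVID stop lie between the windows |
| (b) Just before the 2021 restart | After the 2021 restart | Baseline lies in the COVID interruption and follows the first run |
| (c) Before end of 2019 | First run, until the stop | No COVID pause between the windows, but the recommenced trial is not evaluated; length of this run not stated |

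Only (a) and (b) bear on the restarted trial. In both, a change is mixed with calendar time. In (b) it is also mixed with earlier exposure.

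**3. How much could it matter?** All inputs here are assumptions: equal windows, Poisson counts, a true DIvERT effect of zero, *m* Code Greys expected before, and a background rate ratio *r*.

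*Uncontrolled test.* With A ~ Poisson(m) before and B ~ Poisson(m·r) after, the exact conditional test treats A as Binomial(A+B, 0.5). It is two-sided at 5%, with 40,000 simulated trials per cell.

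*With a comparison ward* (counts C before, D after) that has the same *m* and the same *r*: z = [ln(B/A) − ln(D/C)] / √(1/A + 1/B + 1/C + 1/D), rejecting if |z| > 1.96.

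| m | r = 1.0 | r = 0.9 | r = 0.8 | r = 0.7 | with comparison ward, these r |
|---|---|---|---|---|---|
| 30 | 3.7% | 5.2% | 10.6% | 20.3% | 4.8–5.1% |
| 60 | 3.9% | 7.3% | 18.7% | 38.8% | 4.8–5.2% |
| 120 | 4.2% | 11.0% | 34.6% | 69.5% | 4.9–5.2% |
| 240 | 4.5% | 19.0% | 62.1% | 94.2% | 4.9–5.0% |

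A background rise works the same way. At r = 1.2 the uncontrolled test rejects in 9.2% (m = 30) to 53.6% (m = 240) of trials.

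*Closed-form cross-check.* With n events before and rate ratio R, SE = √(1/n + 1/(nR)), and the rejection probability is Φ(|ln R|/SE − 1.96) + Φ(−|ln R|/SE − 1.96). For n = 160 and R = 0.8, SE = √(0.00625 + 0.0078125) = 0.1186, |ln 0.8| = 0.2231 and the ratio is 1.88, which gives 0.47. At n = 40, 80, 160 and 320 the values are 0.16, 0.27, 0.47 and 0.76 for R = 0.8, and 0.30, 0.53, 0.83 and 0.98 for R = 0.7.

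**4. Reading the table.** In these scenarios the rate really does differ between periods, so the test is not wrong about that. The error lies in assigning the difference to DIvERT. More events make this error more likely, so lengthening the audit window does not cure it. The figure near 5% with a comparison ward follows from assuming that the ward shares the background change. It shows what a suitable comparator buys, not that one exists here.

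**The case against.** The strongest reply is that this test carries limited weight. The Aim makes causal explanation the primary objective: how DIvERT works, for whom and in what circumstances. The Realist evaluation section sets this against asking simply whether something works, and Step 5 asks for modest claims. The stated aim is to test for a difference, not to attribute it. This stands, and it lowers the weight of the point. It does not remove the confounding: interviews, observations and a survey can explain mechanisms, but they do not correct a comparison of counts across calendar time.

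A reader might go further than the documents allow in four ways.

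- *That the comparison is known to span the COVID stop.* No section dates the windows or names the wards for the test, and comparison (c) would avoid the pause. The length of the first run is not given, so the degree of earlier exposure is unknown.
- *That adoption turns on this test.* The Method section makes adoption conditional on success, but does not define success or link it to Code Grey.
- *That the analysis lacks a bed-day denominator or mishandles repeat calls by one patient.* The article condenses a fuller plan that is not shown. Denominators, count models and repeat events are commonly left to such a plan, and their absence here is no finding.
- *That the percentages above estimate the bias in this study.* They rest on assumed counts and assumed background changes. The documents show neither the size nor the direction of any change.

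It is also fair to say that an elaborate segmented model may not be estimable from two specialised settings and an audit that may last only six months. Nor is it shown that other wards shared their pandemic-era changes.

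**Conclusion.** The point holds for this test taken alone. The article fixes a before/after contrast, mentions no concurrent comparator, and reports a start, a COVID stop and a restart. Both baselines that could serve the restarted trial are confounded, one by the first run and the pandemic in between, the other by a COVID-period baseline after earlier exposure. Because the windows are undated, this is an inference from the timeline, but it does not depend on which of the two is chosen.

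The size cannot be determined from the documents. Under the stated assumptions, with background falls of 10% to 30% and 30 to 240 events in the before window, a nominal 5% test would wrongly suggest a DIvERT effect in 5% to 94% of trials. The conclusion does not rest on those figures. The matter is worth correcting before the Code Grey result is interpreted. It does not undermine the realist evaluation as a whole.

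**What to change.** Under Quantitative data analysis, define the comparison as follows:

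- *Before:* a dated period preceding the end-2019 start.
- *Separate phases:* the first run and the COVID pause, each shown on its own and not counted as before.
- *After:* a dated period from the 2021 restart.
- *Comparator:* the change over the same dates in concurrent non-pilot wards, taken from the same Code Grey database, with reasons why those wards are comparable. Where the data allow, a monthly time series of Code Grey rates is an alternative.
- *Fallback:* if neither suitable wards nor an adequate series is available, report the Code Grey change as descriptive, with no effectiveness wording.

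The cost is extraction of existing records for more months and some further wards, plus modest extra analysis. It needs no new participants or procedures. The interval will be wider. If the comparison wards contribute k times the pilot wards' events, the standard error of the log ratio grows by about √(1 + 1/k), which is 1.41 for k = 1 and 1.12 for k = 4 (Poisson counts, same background change). The claim will also be more modest.
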